## 3.5. Sample size

Two controls will be selected for each case. In order to identify an Odds Ratio of at least 1.5 with a power of 80% for risk factors present in 30% of the control population, a sample size of 320 cases and 640 controls was calculated.

## 3.6. Sampling procedure

A representative sample of cases will be selected by random sampling, using random numbers generated in MS Excel, from a line list of cases who are living within the 7 “aires de santé” believed to be hotspots of TF transmission within Kikwit. Controls will be selected in two phases.

In the first phase, a geo-referenced polygon around each of the the 7 “aires de sante” will be generated from images obtained from Google Earth. Then with the help of the software package R, a total of 1500 random points will be generated within this polygon and the geographic coordinates of each point will be registered. Again, with the help of Google Earth images, all the points not falling on the roof of a house will be eliminated. Finally, 640 houses will be selected at random from the remaining points and allocated to cases: the first and the second point will be allocated to case 1, the third and fourth to case 2, and so on. As such, each case of the study population will have 2 random points allocated that each correspond to a house within the polygon.

In the second phase, with the help of a GPS, the corresponding houses will be visited by field teams. Within the household, a control will be recruited, matching the corresponding case in sex and age, and without suspicion of TF during the study period. If within this household no one matches the case or no one corresponds to the control criteria, then the field team will survey the next occupied building to the right. A household is defined as a group of people sleeping in the house and sharing the meals regularly during the study period.

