In week 46 of 2011, or five years after the first recorded outbreak, a second outbreak of TF occurred in Kikwit. Between November 14th and December 25th 2011, a total of 1438 cases were reported, of which 13 (1%) were confirmed by laboratory diagnosis: 6 were positive for *Salmonella* Typhi on 16 hemocultures and 7 were positive for *Salmonella* Typhi on 13 coprocultures. A total of 18 samples were rejected for analysis as not transported correctly. In total, 1367 simple TF cases and 71 cases with peritonitis and intestinal perforation were registered and approximately 22 patients have died (fatality rate 1,53 %).

Figure 2 shows the epidemic curve for the Typhoid Fever outbreak from November 14th until 25th December 2011.

Figures from the outbreak in 2006 and 2011 show an increase in cases of the disease at the beginning of the rainy season. Apart from this cyclic nature it can also be observed that in 2006 and 2011, the same geographic zones were systematically touched most; in these zones, a population of about 60,000 out of the 350,000 inhabitants of Kikwit are living. This information suggests that the TF outbreaks might be associated with a structural problem within a potential high TF risk zone in Kikwit. This hypothesis, that 7 out of the 33 “aires de santé” represent a hotspot of TF transmission within Kikwit, is currently the topic of a parallel focused investigation.

[figure not shown]

Figure 3: map of Kikwit Nord with hotspots of transmissions in 2006 and 2011 outbreaks

In Kikwit access to safe water is a challenge, and water source contamination is one of the most cited risk factors in a TF outbreak5. During the rainy season, where there is either no sewage disposal or working sewer system, runoff of rains follows the slopes down to the Lukemi River and contaminates open water sources used by the population of “Kikwit ville basse”, the lower lying part of town, with excreta. Even water produced at the borehole of Regisdeso at “Kikwit ville basse”, and sold to those who can afford it, might be contaminated. Chlorine is not adequately applied and as the water pressure in the outdated and leaking network is not constant, the contaminated surface water is sucked into the pipes the moment the pressure drops.

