**3. Methods**

3.1. Study Design:

A observational case-control study with individual matching for age and sex.

3.2. Setting:

Kikwit is the largest city of [Bandundu Province](http://en.wikipedia.org/wiki/Bandundu_(province)), lying on the [Kwilu River](http://en.wikipedia.org/wiki/Kwilu_River) in the southwestern part of the [DRC](http://en.wikipedia.org/wiki/Democratic_Republic_of_Congo). The population is approximately 350,000. The situation in DRC is dramatic in terms of health provision, with a weak health system, extremely poor accessibility of the existing health system and regular emergency levels of mortality figures, even in stable districts. These negative indicators are the result of, amongst others, decades of civil war and unrest, poor infrastructure and challenging geographical features, and poor management of the existing resources.

The sanitary district of Kikwit lies about 500 kilometers east of the capital, Kinshasa. It has a supervisee of 330 km² and a population density of approximately 1282 habitants per km². It is composed of 2 “zones de santé”:

- ZS de Kikwit Nord (161,046 habitants), 18 “aires de santé”, comprising 2 communes: Lukolela et Nzinda.
- ZS de Kikwit Sud (176,300 habitants), 15 “aires de santé”, comprising 2 communes: Lukeni et Kazamba

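### If 1500 is the total number of random points, 640 houses need about 43% roof cover; a shortfall is likely, no rule covers it, and pooled allocation does not secure same-aire controls

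*Protocol*

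**What the plan says.** Section 3.5 sets the target: "a sample size of 320 cases and 640 controls was calculated". Section 3.6 describes how the 640 control houses are found:

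- The mapping step draws "a geo-referenced polygon around each of the the 7" *aires de santé* regarded as hotspots.
- The next step refers to a single polygon: "a total of 1500 random points will be generated within this polygon".
- On satellite images, "all the points not falling on the roof of a house will be eliminated".
- Then "640 houses will be selected at random from the remaining points and allocated to cases", with points 1 and 2 going to case 1, points 3 and 4 to case 2, and so on.
- In the field, if a visited house yields no suitable control, "then the field team will survey the next occupied building to the right".

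Section 3.4 requires each control to share the case's sex, age class and *aire de santé*. Sections 3.1 and 3.6 name only age and sex as matching factors.

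The protocol states no expected share of points on roofs, no land area for the seven *aires*, and no step to follow if fewer than 640 points remain.

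**The concern.** A uniform random point falls on a roof with probability equal to the share of land under roofs. The land inside the boundaries includes slopes, small rivers, springs and paths as well as houses. Asking for 640 houses out of 1500 points therefore assumes a high roof share, and choosing 640 at random from the remainder assumes a surplus beyond that. Neither assumption is stated or supported.

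Two things are at stake. First, if fewer than 640 points remain, the written procedure stops short of its target. The only replacement rule applies after a house has been visited and found unsuitable, so the way of making up the number is left to whoever does the mapping. Second, allocation by list position takes no account of which *aire* a point lies in. A case in one *aire* can be given two houses in another, contrary to the matching in section 3.4. That affects the set of controls against which each case's water source and sanitation are compared.

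**Working it through.** **Inputs from the protocol.** 1500 points, 7 polygons, 640 houses and the roof-only rule (section 3.6); 320 cases and 640 controls, odds ratio 1.5, 30% exposure in controls, 80% power (section 3.5); about 60,000 people in the hotspot zones (section 1).

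**Assumptions, not in the protocol.** Two-sided alpha 0.05; hotspot density 5,000 to 20,000 persons per km²; 5 to 15 m² of roof per person.

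**1. The target of 640.** Exposure in cases is 1.5 × 0.30 / (1 + 0.30 × 0.5) = 0.3913. The pooled two-proportion formula with two controls per case gives 316 cases and 632 controls; power at 320/640 is 80.5%. The plan's figure is reproduced closely, so 640 is a sound target for the draw.

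**2. Roof share needed.**

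- 1500 points in all: 640/1500 = 42.7%.
- 1500 points in each of 7 polygons: 640/10,500 = 6.1%.

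The number of roof points is binomial. For 1500 points:

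| Roof share | Expected roof points | P(at least 640) |
|---|---|---|
| 30% | 450 | about 2 × 10⁻²⁵ |
| 40% | 600 | 0.019 |
| 42.7% | 640 | 0.51 |
| 45% | 675 | 0.97 |

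A 95% chance needs 44.7% (6.5% with 10,500 points). These are counts of points. Two points on one roof give one house, so the share needed for 640 distinct houses is slightly higher.

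**3. Plausible yield.** Roof share = density × roof area per person / 1,000,000 m². Expected roof points = 1500 × share.

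| Persons per km² | 5 m² | 10 m² | 15 m² |
|---|---|---|---|
| 5,000 | 2.5% (38 points) | 5% (75) | 7.5% (113) |
| 10,000 | 5% (75) | 10% (150) | 15% (225) |
| 20,000 | 10% (150) | 20% (300) | 30% (450) |

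Every cell is below 640. Going beyond this range, 30,000 per km² with 15 m² gives 45% (675 points), which would do. At 15 m² per person, 42.7% cover needs 426,667/15 = 28,444 persons per km², which puts all 60,000 people on 60,000/28,444 = 2.1 km².

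With 10,500 points, six of the nine cells exceed 6.1%. The other three (2.5%, 5% and 5%) give 263, 525 and 525 points.

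**4. Points needed for an expected 640 hits.** 640/share: 6,400 at 10%, 3,200 at 20%, 2,134 at 30%. No single fixed number suits an unknown roof share.

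**5. Matching on *aire*.** Suppose the 640 houses are in random order and either the cases or the houses are spread evenly over the seven *aires*. A given house then lies in its case's *aire* with probability 1/7, about 14%. This is only an illustration, since the protocol does not state the order of the list or the spread. It shows that allocation by list position alone does not deliver the match.

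**The case against.** The strongest reply is that the text can be read as 1500 points in each polygon. A polygon is drawn around each *aire*, and the next sentence speaks of points inside this polygon, in the singular. On that reading 6.1% cover suffices, and selecting 640 from the remainder makes sense. This stands as a possible reading. The reference to a total favours a single set, and the required cover differs sevenfold between the two, so the text has to say which applies.

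A second reply is that a shortage would be seen at the desk, before any house is visited, and met by generating more points. That also stands. It answers the stronger inference that field teams would fill gaps by convenience and that the 80% power would be lost: nothing in the protocol says so. It does not supply the missing rule.

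A reader might go further and infer that the sample cannot be drawn at all, pointing to the "population density of approximately 1282 habitants per km²" in section 3.2. The documents do not support that. The figure is an average for a 330 km² district, not for the hotspots. It also disagrees with the same section's populations: 161,046 + 176,300 = 337,346, and 337,346/330 = 1,022 per km². Roof cover in the seven *aires* is not given, and very dense settlement could approach 43%.

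A reader might also infer that roof-based selection favours wealthier households. Uniform points do hit roofs in proportion to their area, but the protocol does not link roof size to wealth, piped water or latrines. Accepting roofs with probability inverse to area would be a trade-off. One person is recruited per house, so if larger roofs shelter more people, area-proportional selection partly offsets each person's lower chance within the house.

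**Conclusion.** The point holds as a likely shortfall and a gap in the rule, not as an impossibility. With 1500 points in total, 640 houses need about 43% roof cover, or about 45% for a 95% chance, and slightly more once repeat hits on one roof are removed. Under the assumed densities and roof areas, about 40 to 450 points would be kept. That range rests on assumptions from outside the protocol; the 42.7% is the protocol's own arithmetic on the single-set reading. If 1500 per *aire* was meant, 6.1% suffices and a shortfall arises only at the low end of the assumed range.

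Two defects do not depend on roof cover or on the 43% figure. No rule says how to obtain more points when too few fall on roofs, and allocation by list position does not secure the same-*aire* matching of section 3.4. The change is worth making before the draw. No loss of power and no wealth bias has been shown.

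**What to change.** In section 3.6, replace the fixed 1500 points and the pooled allocation with a sequential draw within each *aire de santé*:

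1. Sample the 320 cases first and count them by *aire*, using the line-list address.
2. In each *aire*, generate random points in R one after another, keeping those that fall on a house roof not already hit.
3. Stop when the number kept equals twice the sampled cases in that *aire* plus an ordered reserve of stated size. Over the seven *aires* the main list then totals 2 × 320 = 640 houses.
4. Allocate the points, in the order drawn, only to cases of the same *aire*. State when the reserve is used and how it relates to the existing next-building rule.
5. Name *aire de santé* as a matching factor in sections 3.1 and 3.6, in line with section 3.4.

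This settles the reading of 1500, guarantees the number of houses whatever the roof cover, and delivers the matching. It costs a little more desk time in R and on the satellite images, and no extra fieldwork.

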## 3.4. Study population

The study population consisted of TF cases randomly selected from the line list of cases who are living within 7 out of the 33 “aires de santé”, believed to be hotspots of TF transmission within Kikwit.

The case definition during the outbreak was provided jointly by the Ministry of Health and the World Health Organization. A **Suspected case** is any person with gradual onset of steadily increasing and then persistently high fever, malaise, headache, sore throat, cough, and, sometimes, abdominal pain and constipation or diarrhea. A **Confirmed case** is asuspected case confirmed by isolation of *Salmonella* Typhi from blood, bone marrow, duodenal fluid or stool. For the confirmation of TF, isolation of *Salmonella* Typhi is required. Blood culture is the mainstay of the diagnosis. In endemic areas, stool isolation alone is insufficient for diagnosis if the clinical picture is not complete.

Two controls of the same sex, age class (10 to 14, 15 to 19, 20 to 29, 30 to 39, 40 to 49 and more than 50) and “aire de santé” will be selected per case. Selection criteria for controls are not having been suspected of TF during the study period and having the possibility to present themselves at the health structure during the study period if required.

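### Section 3.4 requires controls matched on aire de santé, but the allocation rule in section 3.6 ignores aire, so the stated match is not delivered

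*Protocol*

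**What the plan says.** Three sections of the protocol describe the matching.

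- **Section 3.1 (Study Design):** "A observational case-control study with individual matching for age and sex". Aire is not named.
- **Section 3.4 (Study population):** two controls of the same sex and age class "and “aire de santé” will be selected per case". Aire is a third matching factor here.
- **Section 3.6 (Sampling procedure):** the only operating instructions. The steps are:
  1. "a geo-referenced polygon around each of the the 7 “aires de sante” will be generated".
  2. "a total of 1500 random points will be generated within this polygon".
  3. Points that do not fall on a roof are discarded.
  4. "640 houses will be selected at random from the remaining points and allocated to cases".
  5. Allocation follows list order: "the first and the second point will be allocated to case 1, the third and fourth to case 2, and so on".
  6. At the house, the team recruits a control "matching the corresponding case in sex and age, and without suspicion of TF during the study period".
  7. If nobody qualifies, the team moves to the adjacent occupied building on the right.

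Cases are a random sample from the line list across the same 7 aires. No step in section 3.6 sorts or restricts points or cases by aire.

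**The concern.** Section 3.4 promises a match on location that the procedure in section 3.6 cannot produce except by chance. A field team could follow section 3.6 exactly and still breach section 3.4 for most controls.

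Location is not incidental here. The introduction attributes the outbreaks to particular zones. Section 3.2 describes unprotected springs identified aire by aire, and poorer water access in the lower town. Water source, storage and sanitation are among the main study variables (section 3.12). Among the 7 aires, sampled cases follow incidence, while control houses follow where random points hit roofs. Where those two distributions differ and an exposure also differs by aire, an odds ratio that ignores aire mixes the effect of the exposure with the effect of location. Anyone relying on section 3.4 would believe the design had already dealt with this.

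**Working it through.** **The plan's own figure.** Section 3.5 gives 320 cases and 640 controls for an odds ratio (OR) of 1.5, 30% exposure in controls and 80% power. Two-sided 5% is assumed, since no alpha is stated.

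- Exposure in cases: p1 = 1.5 × 0.30 / (0.70 + 1.5 × 0.30) = 0.45 / 1.15 = 0.391.
- Mean exposure: (0.391 + 2 × 0.30) / 3 = 0.330.
- n = [1.96 √(1.5 × 0.330 × 0.670) + 0.842 √(0.391 × 0.609 + 0.30 × 0.70 / 2)]² / 0.0913² = (1.129 + 0.493)² / 0.00834 ≈ 316 cases.

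The stated 320 therefore reproduces closely. It also fixes 640 as the whole control sample (2 × 320).

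**Could section 3.6 be meant to run separately per aire?** Its first step speaks of a polygon around each aire. But 640 is the total number of controls, and drawing 640 in each of 7 polygons would give 7 × 640 = 4,480. Points and cases are each numbered as one sequence, and the 1500 points are a total. Even if seven polygons are drawn, the retained points are pooled before allocation.

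**Chance of an aire match.** Let c_k be the share of sampled cases in aire k and h_k the share of selected houses. When allocation ignores aire, the expected share of controls in their case's aire is Σ c_k h_k. The protocol gives neither set of shares, so all rows below are assumptions.

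| Assumed distribution | Σ c_k h_k | Controls of 640 |
|---|---|---|
| Houses equal over 7 aires, cases any | 1/7 = 14.3% | 91 |
| Cases and houses both 30/20/15/12/10/8/5% | 0.0900 + 0.0400 + 0.0225 + 0.0144 + 0.0100 + 0.0064 + 0.0025 = 18.6% | 119 |
| One aire has 30% of both, rest equal | 0.3² + 0.7²/6 = 17.2% | 110 |
| One aire has 50% of both, rest equal | 0.5² + 0.5²/6 = 29.2% | 187 |
| One aire has 60% of both, rest equal | 0.6² + 0.4²/6 = 38.7% | 247 |

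With equal shares, both controls match in (1/7)² = 2.0% of sets, about 6.5 of 320. In the dominant-aire pattern the match rate passes 50% only if one aire holds about 70% of both cases and houses. If each house were allocated within its case's aire, all 640 starting houses would match.

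**What it could do to an odds ratio.** This is an illustration, not a prediction. Assume exposure among non-cases falls in even steps from 50% to 10% over the 7 aires (50.0, 43.3, 36.7, 30.0, 23.3, 16.7, 10.0), with cases distributed 30/20/15/12/10/8/5% and no adjustment for aire. For a null factor, case exposure is Σ c_k e_k = 0.369, so the odds are 0.369 / 0.631 = 0.586.

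| Control houses | Control exposure | Crude OR, null factor | Crude OR, true OR 1.5 |
|---|---|---|---|
| Distributed like the cases | 0.369 | 0.586 / 0.586 = 1.00 | 1.46 |
| Halfway to equal shares | 0.335 | 0.586 / 0.503 = 1.16 | 1.70 |
| Equal shares | 0.300 | 0.586 / 0.429 = 1.37 | 1.99 |

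For the last column, each aire's case exposure is 1.5e / (1 − e + 1.5e), and the weighted mean is 0.461. The result runs from slight attenuation to clear inflation, depending on distributions the documents do not give.

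**The case against.** The strongest reply is that failing to match is not the same as confounding. Cases and control houses come from the same 7 aires, so the pooled draw is still a usable area-wide control sample. Section 3.6 registers the coordinates of each point, section 3.9 says the line list holds addresses, and section 3.13 plans multivariate analysis. Aire can therefore be derived and adjusted for. All of this stands. It limits the harm, but it does not make section 3.4 true.

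Two stronger readings are tempting, and the documents do not support them.

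- **That aire confounds every water and sanitation odds ratio.** The introduction and section 3.2 describe one central market and a piped network that is not divided by aire. Section 3.2 also reports up to four or five springs per aire, so exposure varies within aires. Only factors whose prevalence differs by aire are at risk, and only if cases and houses are distributed differently.
- **That the analysis will wrongly treat the sets as location-matched.** Section 3.13 names bivariate and multivariate analysis and does not commit to analysis by matched set. The statistical analysis plan is not at hand.

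It can also be said that matching on aire is not obviously better. The aim is to find risk factors, including water source, and close matching on location removes between-aire contrast. That is a fair reason to offer two remedies. It is not a reason to leave the three sections in disagreement.

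**Conclusion.** The inconsistency is real. Section 3.4 makes aire a matching factor; sections 3.1 and 3.6 do not, and section 3.6 followed literally delivers the match only by chance. The expected match rate is about 14% (91 of 640) with equal house shares, 19% with moderately skewed shares, and 39% with one aire holding 60% of both cases and houses. That most controls would be unmatched on aire is conditional on these assumed distributions, but in the dominant-aire pattern it fails only near a 70% share.

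The consequence for the estimates is possible confounding by location, of unknown size: none for a null factor if cases and houses are distributed alike over the aires, and material if they are not and aire is ignored. It does not make the control group unusable, and it does not change the stated sample size.

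**What to change.** Choose one route and state the same matching factors in sections 3.1, 3.4 and 3.6.

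1. **Keep aire as a matching factor.** Before fieldwork, for each aire k with n_k sampled cases, select 2 × n_k houses plus an ordered reserve from the retained points in that aire. Allocate them only to that aire's cases, and keep the adjacent-building substitution inside the aire. Generate further points if an aire falls short: with equal aires, the 1500 points give about 214 per aire, of which about 91 must be on roofs and selected.
2. **Drop aire from section 3.4.** Derive aire for every control from the registered coordinates and for every case from the line-list address, keep it as a variable when identifiers are removed, and name it as an adjustment factor in the multivariate analysis of section 3.13.

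Route 1 costs protocol wording and a few lines of R, with no extra participants; it is not available once houses have been visited. It may cost some power, because controls from the same aire tend to share exposures with their case. A matched-set calculation needs 316 cases at an exposure correlation of 0, 328 at 0.05 and 342 at 0.1, and the protocol states no correlation. Route 2 costs wording and one derived variable, and remains open after fieldwork as long as locations are retained.

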3.9. Sources of data

Sources of data are as follows: official data from the Ministry of Health registers (line list) will be used to describe the previous epidemics in terms of person, time and place. This line list has been created by the MOH in order to register every suspected case of TF, and contains several items of interest such as name, address, sex, age, date of onset, date of admission, symptoms at admission, status, results of laboratory analysis and outcome.

Population data (denominators) used for rate estimations will be obtained from the census bureau in Kikwit.

Complementary sources of information will be:

- interviews with the health authorities of the concerned area.
- environmental evaluations in the most affected area’s.
- visit to the reference hospital.
- visit to the reference laboratory.
- chemical and biological water tests.

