## 3.12. Variables

For each respondent, all variables contained in the survey questionnaire will be collected. The study is centered on demographics and household composition, household water sourcing and storage, hygiene practices, and food/drink hygiene practices. The variables collected are listed in full in the questionnaire in Annex I. Additionally, variables pertaining to water quality will be collected per household (cf. §3.10.).

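### Cases are sampled as persons but one control is taken per house, so controls under-represent people who live with others of their own sex and age class

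*Protocol*

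**What the plan says.** The two arms of the study are sampled in different units.

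- **Cases.** Section 3.6: "A representative sample of cases will be selected by random sampling, using random numbers generated in MS Excel, from a line list of cases". Section 3.9 describes that list: "This line list has been created by the MOH in order to register every suspected case of TF". The unit is the person.
- **Controls, first phase.** Random points are generated within the polygons, and "all the points not falling on the roof of a house will be eliminated". Then "640 houses will be selected at random from the remaining points and allocated to cases". The unit is the house, and a house's chance of selection follows its roof area.
- **Controls, second phase.** "Within the household, a control will be recruited, matching the corresponding case in sex and age". If nobody in the house qualifies, "then the field team will survey the next occupied building to the right".

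Section 3.6 does not say which resident to take when several qualify, and does not ask the team to count them. Section 3.13 names bivariate and multivariate analysis and no selection weight. Section 3.12 gives household composition a central place: "The study is centered on demographics and household composition".

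**The concern.** Suppose a house holds k people of a given sex and age class. If disease is unrelated to household composition, that house supplies cases in proportion to k. It supplies at most one control, so each of its k residents has a 1/k chance once the team is inside. People who live with same-class peers are therefore rarer among controls than in the population that gave rise to the cases.

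Matching on sex, age class and health area (section 3.4) does not remove this. It fixes the class, but not how many members of that class share the house. Random placement of the points does not remove it either, because the distortion arises inside the house.

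At stake is a spurious association for shared living, in a study meant to identify transmission risk factors and guide interventions. An odds ratio near 2 for living with a peer could be read as person-to-person spread within the home.

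**Working it through.** **The plan's own figure.** Section 3.5 gives 320 cases and 640 controls for an odds ratio (OR) of 1.5, 30% exposure in controls, 80% power and two controls per case. Exposure in cases is then 1.5×0.30/(0.70+1.5×0.30) = 0.391. The two-proportion formula (two-sided 5% assumed, no continuity correction) gives 316 and 632. Power at 320/640 is 80.5%. The figure reproduces, and this point does not change it.

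**Equal house selection.** Let f(k) be the share of houses with k residents in the matched class. With no true effect:

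- Cases, odds of k≥2 against k=1: Σ k f(k) / f(1), summed over k≥2.
- Controls, same odds: Σ f(k) / f(1), summed over k≥2.
- Ratio: Σ k f(k) / Σ f(k) over k≥2, which is the mean of k among houses with at least two such residents.

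That mean cannot be below 2. If house selection ignores size, the false OR is therefore at least 2 whatever the household size distribution. Only the excess above 2 depends on assumptions.

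**One scenario by hand.** Assume household size N = 1 + Poisson(6), so mean 7, and class share q = 0.10.

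- E(k) = 7×0.10 = 0.700.
- P(k=1) = 0.10×e^(−0.6)×(1+5.4) = 0.351.
- P(k≥1) = 1 − 0.9×e^(−0.6) = 0.506.
- Cases with k≥2: 1 − 0.351/0.700 = 49.8%.
- Controls with k≥2: 1 − 0.351/0.506 = 30.6%.
- OR = (0.498/0.502)/(0.306/0.694) = 2.25. A simulation of the same scenario also gives 2.25.

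**Range.** Assumptions, none in the documents: mean household size 5.5 to 7.5; class share 4% to 10%; Poisson or negative binomial sizes; class membership independent between residents.

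| House selection | False OR, k≥2 against 1 |
|---|---|
| Ignores household size | 2.07 to 2.35 |
| First house proportional to size, replacement house not | 1.93 to 2.10 |
| Every house proportional to size | 1.62 to 1.98 |

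The middle row matters because under these assumptions about 40% to 80% of first-visited houses have nobody in the class. Many controls then come from the next building, which is not chosen by roof area. A separate set of assumptions (mean 5 or 7, share 4% to 15%, Poisson) gives 2.0 to 2.4, and a chance of about 93% or more that 320/640 would find the false association significant.

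**Total household size.** For eight or more residents against fewer, the false OR is about 1.1 to 1.3 if house selection ignores size. It is 0.85 to 0.94 if the first house is proportional to size, and lower still (down to about 0.5) if every house is.

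**Variables loosely tied to k.** If an exposure has prevalence 30% at k=1 and 40% at k≥2, the false OR is 1.03 to 1.10. At 50% for k≥2 it is 1.07 to 1.19. In the hand scenario with 40%, exposure is 0.30+0.10×0.498 = 0.350 in cases and 0.30+0.10×0.306 = 0.331 in controls, so OR = 1.09.

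**Does the correction work?** With house selection unrelated to size, a log(k) offset (simulated) or a weight of k returns an OR of 1.00 for k≥2. With the first house proportional to size (mean 5 or 7, share 4% to 15%), the weighted OR for k≥2 is 0.88 to 0.97. For total size under that selection, and the 5.5 to 7.5 and 4% to 10% assumptions, weighting moves the OR from 0.85–0.94 to 0.63–0.88, further from 1.

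**The case against.** Four objections deserve weight.

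- **Scope.** A reader might infer that members of large households in general are under-represented, so that household size itself will look like a risk factor. The documents do not support this. The bias runs through k, the count in one sex and age class. Selection by roof point favours larger houses if roof area grows with household size, and can cancel or reverse the effect on total size. This objection stands.
- **Reach.** A reader might also infer that shared cups, storage or latrines are biased as strongly. Nothing in the protocol shows how closely these track k, and with modest links the shift is small. Nor does the protocol text name a same-class co-resident variable; section 3.12 refers only to household composition. This stands too.
- **Unseen material.** The questionnaire (Annex I) is not shown, and sections 3.8 and 3.12 say household-level data are collected. An age and sex roster would allow k to be derived approximately, and a weight or offset could sit in an analysis plan. That is fair, so it cannot be said that k will go unrecorded. But a roster cannot supply a random choice within the house. That has to be made in the field, and section 3.6 is where it would be laid down.
- **Assumptions.** Household sizes and class shares are not in the documents. This limits the precise figures. It does not affect the direction for same-class co-residence, which held in every scenario, or the floor of 2 under equal house selection.

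**Conclusion.** The point holds for same-class co-residence. Followed as written, section 3.6 makes living with someone of one's own sex and age class look like a risk factor when it has no effect. The false OR is about 2.0 to 2.35 if house selection ignores household size and about 1.6 to 2.1 if it is proportional to size. Both exceed the 1.5 the study is sized to detect. The figures rest on an assumed mean household size of 5.5 to 7.5 and class share of 4% to 10%.

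It does not extend to a general claim about household size, where neither sign nor size is established, or to water, hygiene and food factors, which shift little unless they follow k closely. The point is worth correcting because household composition is a declared focus and the remedy is cheap, but it does not undermine the study as a whole.

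**What to change.** In section 3.6: on reaching a house, list all residents who meet the case's sex and age class and the control criteria, choose one by random number, and record k. In case households, record the same count (case included) and total household size.

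In section 3.13: for variables defined by same-class co-residence, enter log(k) as an offset in the case-control model or weight controls by k. For total household size and crowding, report results with and without the k correction, in a sensitivity analysis that also considers roof-area selection. The k correction should not be applied to those variables on its own, because it can move them further from the null.

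Cost: one or two lines on the form and one model term. If weights are used instead of the offset, control variance rises by E(k²)/E(k)², about 1.1 to 1.25 under the same assumptions.
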